## Abstract

**Background:**

Considering the high burden of disease of psychosocial problems in children and adolescents, early intervention regarding problem behaviour of young children is very important. The Preventive Child Healthcare (PCH) offers a good setting to detect such problem behaviour and to provide parenting support to the parents concerned. This paper aims to describe the design of an effectiveness study of a parenting programme for parents of children with mild psychosocial problems after an initial, evidence based screening in routine PCH.

**Methods/Design:**

The effects of the intervention will be studied in a randomised controlled trial. Prior to a routine PCH health examination, parents complete a screening questionnaire on psychosocial problems. Parents of children with increased but still subclinical levels of psychosocial problems will be assigned at random to the experimental group (Triple P, level 3) or to the control group (care as usual). Outcome measures, such as problem behaviour in the child and parenting behaviour, will be assessed before, directly after and 6 and 12 months after the intervention.

**Discussion:**

Parenting support may be an effective intervention to reduce psychosocial problems in children but evidence-based parenting programmes that fit the needs of the PCH are not available as yet. Although the Triple P programme seems promising and suitable for a universal population approach, evidence on its effectiveness in routine PCH still lacks.

**Trial registration:**

NTR1338

## Background

Psychosocial problems (e.g. aggressive behaviour, fear, anxiety) frequently occur in children and may lead to serious restrictions in daily functioning currently and in later life, and are the major cause of long-term work disability in young adults [1-3]. Several population-based studies in the Netherlands show that about 20% of all children struggle with psychosocial problems [4,5]. A study in primary and secondary education showed that 13% of all pupils had internalising problems, 11% had externalising problems and 3% had other behavioural problems [6].

Parenting style and child well-being are closely connected which makes parenting support a suitable way to decrease psychosocial problems in young children. Parents can help to prevent these problems in children by teaching them social skills [7]. Therefore methods for early treatment of psychosocial problems in children by enhancing parenting skills become increasingly available [8], but no evidence-based programmes for parenting support are available that suit the child healthcare. Only a minority of the children (13%) with psychosocial problems is under treatment by youth care or youth mental care [4,5,9] whereas early detection and treatment of psychosocial problems in children can improve their prognosis substantially ('the earlier, the better') [4,10,11].

In the Netherlands, Preventive Child Healthcare (PCH) offers an ideal opportunity for the early detection of psychosocial problems among preschool children, comparable to community pediatrics in the USA. In this system, child health professionals (further: CHP), i.e. doctors and nurses, working in preventive child healthcare offer routine well-child care clinics, including the early detection and treatment of psychosocial problems to the entire Dutch population [12,13]. Access is free of charge. This offers an ideal setting to provide parenting support following an evidence-based method of early detection of psychosocial problems in children. For this aim, there is a need for standardised parenting support interventions that are short and suit the competences of CHPs.

Triple P level 3, the so-called Primary Care Triple P, is such a short intervention but evidence for it after an initial screening on psychosocial problems in children in a preventive child healthcare setting still lacks. The intervention consists of practical advice and coaching on managing a specific behavioural problem during four short, individual consultations (20-30 minutes) with parents and their child by a trained child healthcare nurse. It is part of a multilevel system of early intervention for parents of children who have or are at risk of developing behavioural or emotional problems which aims at preventing and decreasing psychosocial problems in children by providing parenting support [14,15]. Research showed that Triple P, including level 3, seems promising when compared with a wait-list control group that receives no help [16]. A quasi-experimental study on the effects of Triple P level 3 in the Netherlands [17] showed significant decreases in the emotional and behavioural problems of children just as effects on parental satisfaction, parental efficacy and overall parental sense of competence. However, a randomised controlled trial investigating the effects of parenting support after an evidence-based, initial screening on psychosocial problems in children has never been done before and long-term follow-up data is currently not available.

### Objective

This paper aims to describe the design of an effectiveness study of a parenting programme for parents of children with mild problem behaviour after an initial screening in routine PCH.

## Methods/Design

### Design

The study is designed as a randomised controlled trial (RCT) with follow-up assessments directly after completion of the intervention, after six months and after twelve months. Eligible families will be randomly assigned to either the Triple P intervention or the care as usual (control) condition. The Medical Ethics Committee of the University Medical Center of Groningen approved the study design, protocols, procedures and informed consent. Participation is voluntary and all participants sign an informed consent form. In order to describe the design of this study, the CONSORT statement is followed [18], a checklist that intends to improve the quality of the reporting of randomised controlled trials.

### Participants

Eligible participants for the trial will be selected from a community sample of parents of 9-11 year old primary school children in the four northern provinces of the Netherlands, who will be examined during their routine PCH screening,. In the Netherlands, the PCH examines almost all children (>90%) at regular times. The four Northern provinces cover approximately 13% of all Dutch children of this age [19].

### Recruitment of study population

Prior to the contact with the PCH, all parents will be asked to complete a screening questionnaire on psychosocial problems in children. As part of the study, we added a baseline questionnaire about parenting behaviour. During routine examination by the PCH, the SDQ (Strengths and Difficulties Questionnaire) [20] total problems score of all children will be computed. Eligible participants, i.e. parents of children with a subclinical SDQ total problems score of 11-13, will be identified and invited by the CHPs to participate in the trial. After informed consent, they will be randomly assigned to the intervention or care as usual group (Figure 1). Families included in the trial will be asked to nominate a primary participating partner who will attend the intervention and complete the accompanying questionnaires. However, both parents are welcome to attend the counseling sessions, which will be carried out at the clinic or at home.

**Figure 1 F1:**
[figure not shown]
**Flowchart of participants**.

### Study inclusion and exclusion criteria

The inclusion criteria are: 1) Age 9 to 11 years, 2) An SDQ total problems score in the subclinical range, i.e. 11-13 [21], 3) Parents must acknowledge mild problem behaviour in their child, 4) Parents are willing to work on their child's psychosocial problems.

The exclusion criteria are: 1) A diagnosis of developmental delay, developmental disorder (e.g. autism), conduct disorder or ADHD in the child, 2) Currently receiving treatment for behavioural problems, 3) A chronic disease for which three or more medical consultations in the past two months have been made, 4) Parental divorce, death or severe disease of someone to whom the child feels attached to (e.g. (grand)parent, sibling, friend, nanny) in the past two months, 5) Parents being in therapy for psychological or relationship problems, 6) Parents being unable to read or speak Dutch, 7) Severe and/or general behavioural or emotional problems beyond the scope of the Triple P level 3 intervention, 8) Suspected parental dysfunction, such as child maltreatment, psychiatric disease, alcohol or drug abuse.

### Randomisation procedure

At the clinic, a research assistant ensures that participants enrolled by CHPs are eligible or have to be excluded from the trial. Randomisation, based on a computer-generated randomisation programme, occurs at the level of individual children in sequence of entrance. To prevent unequal randomisation, participants are pre-stratified and randomised by centre using block randomisation (blocks of six).

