### Sample size

The SDQ will be the primary outcome measure for the power calculation. For an average 3-point decrease in SDQ total problems score, i.e. a change from the subclinical to the normal range, SD = 6 at alpha = 0.05 (two-sided) and beta = 0.20, 64 pairs of children need to be included with an initial SDQ total problems score between 11 and 13. As a loss to follow-up rate of 20% is expected, an initial study population of 80 pairs of children is needed in each treatment group (total: 160). This suffices to show an effect size of 0.5 of the Triple P programme regarding parent-reported child psychosocial problems and parenting problems.

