### Blinding

Participants do not know which research group they will be assigned to. Nurses carrying out the treatment cannot be blinded for the allocated treatment. Since all follow-up questionnaires will be sent by mail, no direct influence by the researchers or the CHPs is likely to occur. After randomisation, all participants receive a research code unknown by the researcher. Therefore, analysis of the data by the researcher will be blind.

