### Analysis

Statistical analysis will be performed according to the 'intention-to-treat' principle. With multiple measurements over time, data on subjects lost to follow-up will be handled by imputation techniques. Change in child behaviour and parenting behaviour will be expressed as standardised effect sizes. To analyse the development of the outcome measures in time, a longitudinal data analysis technique, i.e. random coefficient analysis, will be applied. Baseline characteristics of the parents in the two research groups will be compared using Chi-squared tests for categorical variables, Wilcoxon's test for ordinal variables, and t-tests for continuous variables. Reporting will follow the CONSORT guidelines.

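### A single published block size of six within each centre lets up to a quarter of allocations be foreseen if recruiting staff learn the earlier ones; varying, undisclosed blocks and concealed off-site allocation would largely prevent this

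*Protocol article*

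**What the plan says.** All references are to the protocol article.

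- **Randomisation procedure.** Randomisation "occurs at the level of individual children in sequence of entrance", and "participants are pre-stratified and randomised by centre using block randomisation (blocks of six". Only one block size is given. In addition, "a research assistant ensures that participants enrolled by CHPs are eligible or have to be excluded from the trial", and this person works at the clinic.
- **Sample size.** "80 pairs of children is needed in each treatment group (total: 160" implies 1:1 allocation; no ratio is stated.
- **Recruitment of study population.** Families with a qualifying SDQ score "will be identified and invited by the CHPs to participate in the trial". Consent comes before randomisation.
- **Background.** The recruiting group is defined as "child health professionals (further: CHP), i.e. doctors and nurses" working in preventive child healthcare.
- **Control condition and Intervention.** Usual care is started by a CHP. Triple P is given by specially trained nurses who are employed in the same service.
- **Blinding.** "Nurses carrying out the treatment cannot be blinded for the allocated treatment".
- **Study inclusion and exclusion criteria.** Several criteria are factual or numeric. Others need judgement: whether parents acknowledge the problem, whether they are willing to work on it, whether parental dysfunction is suspected, and whether the child's problems exceed what Triple P level 3 can address.

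**The concern.** In a permuted block, the last allocations are fixed by the ones before them. With one known block size and separate lists per centre, anyone who follows the allocations in a centre can sometimes tell what comes next. Three features make that relevant here. Treatment is open to the nurses who give it. Recruitment and the care of both arms sit in the same service. Entry depends partly on judgement, and one exclusion is defined by the scope of the experimental programme, so a person who expects a Triple P slot might apply it differently from one who expects usual care.

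At stake is selection before randomisation. If families are invited or excluded in the light of the expected arm, the groups can differ in severity or parental motivation. Intention-to-treat analysis does not correct that, and the outcomes rest on parental report, which such differences would affect directly.

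**Working it through.** **Inputs.** Block size six, within centre, in order of entry (Randomisation procedure). Ratio 1:1, implied by 80 + 80, and a total of 160 (Sample size). The number of centres is not given; Strengths and limitations says only that there are several.

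**The plan's own figure.** With a 3-point difference, SD 6, two-sided alpha 0.05 and power 0.80:

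n = 2 × (1.960 + 0.842)² × 6² / 3² = 62.8, i.e. 63 per group; the t-test version gives 63.8, i.e. 64. Allowing for 20% loss, 64 / 0.80 = 80 per group, 160 in total. The stated size is reproduced. The article gives no figure for predictability.

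**Step 1: certain allocations in a block of six.** There are 20 equally likely sequences with three per arm. An allocation is certain once one arm has used its three places.

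- Positions 1 to 3: never certain.
- Position 4: the first three are the same in 2 of 20 sequences, 0.10.
- Position 5: three of the first four are the same in 8 of 20, 0.40.
- Position 6: always, 1.00.

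Sum = 1.5 of 6 = 25%.

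**Step 2: best guess.** Guess the arm with more places left; a tie counts one half. By position, the chance of being right is 0.5, 0.6, 0.6, 0.7, 0.7 and 1.0. Sum = 4.1 of 6 = 68.3%, against 50% by chance.

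**Step 3: number of children.** 160 × 0.25 = 40 if every block were complete. As 160 is not a multiple of six, the most that can occur is 26 complete blocks and four children over: 26 × 1.5 + 0.1 = 39.1. More incomplete blocks across centres would lower this.

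**Step 4: partial knowledge.** Suppose the position in the block is known and each earlier allocation is known independently with probability q (an assumption). Certainty needs all three members of the filled arm to be known, so the share is 0.25 × q³.

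| q | Certain allocations |
|---|---|
| 1 | 25% |
| 0.9 | 18% |
| 0.75 | 11% |
| 0.5 | 3% |
| 0.25 | 0.4% |
| 0 | 0% |

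Simulation gives the same values to rounding.

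**Step 5: varying block sizes.** Simulated (2,000 runs of 60 allocations) for an observer who sees every earlier allocation and knows the set of sizes but not their order.

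| Sizes | Certain | Best guess right |
|---|---|---|
| 6 only | 25.0% | 68.3% |
| 4, 6 | 5.8% | 68.9% |
| 2, 4, 6 | 3.8% | 70.1% |
| 4, 6, 8 | 2.4% | 67.7% |

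Varying the size removes most of the certainty but almost none of the guessing advantage.

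**The case against.** The strongest reply is that the quarter is a worst case. It needs knowledge of the block start and of every earlier allocation in the centre. The Blinding section says that treating nurses are unblinded; it does not say so of recruiters. Time frame of the study mentions training nurses to deliver the programme and training CHPs to recruit as two separate items. Overlap between the two groups is plausible but not stated, and centre sizes are unknown. There are also safeguards: a computer-generated scheme, consent before assignment, and an eligibility check by a research assistant. Who holds the list and how the next allocation is concealed may well be in the full protocol, which is not shown.

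Most of this stands. It turns the 25% into an upper limit and rules out saying that recruiters do foresee allocations. It does not dispose of the point. The fixed size is a stated rule, not an omission. The eligibility check is made at the clinic by a person not described as unaware of earlier allocations. Consent before assignment does not help if the decision to invite or exclude is already coloured by what is expected.

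A reader might also infer that centre, although used for stratification, is dropped from the analysis. The article does not support that. The Analysis section says only that "a longitudinal data analysis technique, i.e. random coefficient analysis, will be applied"; it lists no model terms, and these are commonly left to the analysis plan. Omitting centre would in any case be slightly conservative: with an assumed 2% to 10% of outcome variance between centres, type I error is about 0.048 to 0.039.

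**Conclusion.** The point holds as a cheap improvement to a stated rule. Fixed, published blocks of six within centre allow up to 25% of allocations (at most about 39 of 160 children) to be known in advance. This assumes 1:1 allocation and an observer with full knowledge of block starts and earlier allocations in the centre. With partial knowledge the share falls with the cube of the proportion known, to about 11% at 0.75 and 3% at 0.5.

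It would go too far to conclude that recruiters are unblinded, that selection bias will occur, or that the article presents fixed blocks as a strength. Strengths and limitations credits randomisation in general with reducing selection and allocation bias. That claim would be better supported with less predictable allocation.

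**What to change.** In Randomisation procedure:

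1. Replace the single block size by randomly varying sizes within centre, for example 4, 6 and 8, and do not disclose the sizes to staff or in material that they will read.
2. Generate and hold the list off site, and release each allocation only after eligibility has been recorded. Consent before randomisation is already stated and should stay.
3. Keep earlier allocations in the centre from those who invite or exclude families, including the research assistant who checks eligibility.

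Item 1 alone is not enough, because it leaves the guessing advantage in place; items 2 and 3 address that.

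The cost is small: a setting in the existing randomisation programme and an off-site release step. The statistical downside is a slightly larger possible end-of-trial imbalance within small centres, since an unfinished block of eight can be off by up to four children, against three for a block of six.

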### Sample size

The SDQ will be the primary outcome measure for the power calculation. For an average 3-point decrease in SDQ total problems score, i.e. a change from the subclinical to the normal range, SD = 6 at alpha = 0.05 (two-sided) and beta = 0.20, 64 pairs of children need to be included with an initial SDQ total problems score between 11 and 13. As a loss to follow-up rate of 20% is expected, an initial study population of 80 pairs of children is needed in each treatment group (total: 160). This suffices to show an effect size of 0.5 of the Triple P programme regarding parent-reported child psychosocial problems and parenting problems.

### Blinding

Participants do not know which research group they will be assigned to. Nurses carrying out the treatment cannot be blinded for the allocated treatment. Since all follow-up questionnaires will be sent by mail, no direct influence by the researchers or the CHPs is likely to occur. After randomisation, all participants receive a research code unknown by the researcher. Therefore, analysis of the data by the researcher will be blind.

### Intervention

The intervention to be evaluated is Triple P level 3. Triple P is a multilevel system of family intervention which provides five levels of intervention of increasing strength [22]. Triple P intervention at level 3 (Primary Care Triple P) is a brief, narrow-focus parent programme that is aimed at parents with specific concerns about their child's behaviour or development [23]. It combines advice, rehearsal and self-evaluation to teach parents to manage a discrete child problem behaviour during four individual consultations of 20-30 minutes with the parents and their child (Table 1) [24].

**Table 1 T1:** Overview of Triple P level 3 session content

Session	Contents	Duration
1 Assessment of the presenting problem	Intake interview	15 - 30 minutes
		
	Options for intervention	
		
	Keeping track of the children's behaviour	

2 Developing a parenting plan	Feedback of assessment results	15 - 30 minutes
		
	Causes of child behaviour problems	
		
	Goals for change	
		
	Parenting plan (with active skills training)	

3 Review of implementation	Update on progress	15 - 30 minutes
		
	Refining parenting plan (with active skills training)	
		
	Identifying and overcoming obstacles	
		
	Other issues	

4 Follow-up	Update on progress	15 - 30 minutes
		
	Maintaining progress made	
		
	Other issues	

To ensure the quality of delivery, intervention nurses completed a two-day training course delivered by the Netherlands Youth Institute and the developers of the programme and accreditation in levels 2 and 3 of the Triple P method by an accredited practitioner prior to the start of the project. The professionals conducting the interventions are all nurses employed in the PCH daily practice. Professional adherence to the Triple P method is warranted through several supervision sessions with an accredited practitioner.

### Control condition

Families in the control condition will receive the usual care initiated by a CHP (i.e. a community nurse). Protocols on psychosocial problems of the PCH-organisations prescribe, in case of a deviant SDQ total problem score, that the CHPs verify the gravity of the situation with the parents and, sometimes, with the schoolteacher. If the parents acknowledge the behavioural problems in their child and experience parenting problems, the CHP will try to clarify the problem and provide parenting support (e.g. strategies, tips, tricks). Usually CHPs have three extra contacts at their disposal to provide parenting support. If the problem exceeds the expertise of the CHPs, the parents and child will be referred to a specialist (e.g. psychologist, psychiatrist, child welfare). All CHPs have at least a bachelor's degree in nursing, which means that they have completed four years of education. Most of them also have received a two year specialisation training in community nursing.

### Outcome measures

The primary outcome of the study is problem behaviour of the child after intervention, measured by the (1) Strengths and Difficulties Questionnaire (SDQ) [20], 30 items divided into 5 subscales on prosocial behaviour, hyperactivity, emotional symptoms, conduct problems and peer problems and (2) the Eyberg Child Behavior Inventory (ECBI) [25], 36 items on parental perception of disruptive behaviour including intensity and problem score.

The secondary outcome of the study is parenting behaviour since the intervention aims at parenting as mediator. Parental competence and parenting style will be measured by the (1) Problem Setting and Behaviour Checklist (PSBC) [26], a 28-item rating scale that assesses how confident parents are in dealing with child behaviour problems in various settings and (2) the Parenting Scale (PS) [27], 30 items on parenting behaviour (permissiveness, overreactivity, verbosity). Parenting stress will be measured by (1) the Dutch Parental Stress Index (PSI) [28], 11 items on parenting stress, and (2) the 21-item Depression, Anxiety and Stress Scale (DASS) [29].

At baseline family characteristics will be assessed, i.e.: family situation, age of the parents, parental education, employment and financial situation of the parents, and the ethnicity of the parents and the child.

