### Data collection procedure

Data will be obtained by questionnaires. Participants will be asked to return each of the questionnaires within one week. To minimise loss to follow-up, the parents will be called by phone if the questionnaire has not been returned within one week. The outcome assessments will take place, regard for equal time intervals, directly after treatment (T1), six months (T2) and twelve months (T3) after treatment. Parents who complete all questionnaires will receive a gift voucher.

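### Both the SDQ and the ECBI are named as primary, but the trial is sized on one 5% test of the SDQ total score, and no primary time point or model contrast is designated

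*Protocol article*

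**What the plan says.** All references are to the protocol article.

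- **Outcome measures:** "The primary outcome of the study is problem behaviour of the child after intervention, measured by the (1) Strengths and Difficulties Questionnaire (SDQ") and by the ECBI, described as "36 items on parental perception of disruptive behaviour including intensity and problem score". The SDQ is described by its five subscales. The total problems score is not mentioned here.
- **Sample size:** "The SDQ will be the primary outcome measure for the power calculation". The calculation is on one score: "For an average 3-point decrease in SDQ total problems score", with "SD = 6 at alpha = 0.05 (two-sided) and beta = 0.20". The result is "64 pairs of children need to be included", raised to 80 per group (160 in total) for an expected 20% loss.
- **Data collection procedure:** outcomes are assessed "directly after treatment (T1), six months (T2) and twelve months (T3) after treatment".
- **Analysis:** for development over time, "a longitudinal data analysis technique, i.e. random coefficient analysis, will be applied". The coefficient or contrast that forms the primary test is not identified.

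**The concern.** Outcome measures and Sample size do not agree on what is primary. One lists two instruments with at least three candidate scores (SDQ total, ECBI intensity, ECBI problem). The other allows for one score and spends the whole 5% on it. The phrase placing the primary outcome after the intervention fits the first follow-up, any of the three, or the whole course.

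Two things are at stake. If every stated primary is tested at 5%, the error rate behind the trial's conclusion is higher than the one used for sizing. And a mixed result, such as a benefit on the ECBI directly after treatment with no SDQ difference at twelve months, has no agreed reading, so the headline result could be chosen after the data are seen. The Discussion links a finding of effectiveness to further implementation and to government policy, so the claim needs a fixed basis.

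**Working it through.** **1. The plan's own figure.** Inputs from Sample size: difference 3, SD 6 (so effect size 3/6 = 0.5), two-sided alpha 0.05, power 80%, loss 20%. The word pairs is read as children per group, since the section gives 80 in each group and 160 in total.

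- Normal approximation: n = 2 × (1.96 + 0.84)² × 6²/3², which rounds up to 63 per group.
- Two-sample t-test: 63.77, rounded up to 64 per group.
- Loss: 64 / (1 − 0.20) = 80 per group, 160 in total.
- Power with 64 per group (normal approximation): 80.7%.

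The stated size is reproduced. It fits exactly one test at 5%.

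**2. One longitudinal test per instrument or score.** This is the reading closest to the Analysis section. For k independent tests, the chance of at least one false positive is 1 − 0.95^k. Correlated tests were simulated as two-sided z-tests (400,000 draws). The documents give no correlations, so these are assumptions.

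| Primary tests | Independent | Correlation 0.5 | Correlation 0.7 |
|---|---|---|---|
| 2 (one score per instrument) | 1 − 0.95² = 9.8% | 9.0% | 8.4% |
| 3 (SDQ total, ECBI intensity, ECBI problem) | 1 − 0.95³ = 14.3% | 12.6% | 10.9% |

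The range is about 8-14%. These figures count significant results in either direction. False claims of benefit alone run from 4.2% (two tests, correlation 0.7) to 7.3% (three independent tests), against 2.5% for a single test.

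**3. Nine visit-level tests, for comparison only.** Three scores at three times, success on any one, with the correlation between two tests taken as the between-score times the between-time correlation:

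- independent: 1 − 0.95⁹ = 37.0%
- both correlations 0.5: 29.3%
- both 0.7: 22.6%
- both 0.8: 18.4%

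For false claims of benefit alone, the 0.5 and 0.7 cases give 14.8% and 11.3%.

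**4. What each remedy costs.**

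- One primary test of SDQ total: error 5%; 64 (80 after loss) per group is unchanged.
- Bonferroni over two tests (alpha 0.025): 77 per group, 97 after loss; or 72.1% power with 64.
- Bonferroni over three tests (alpha 0.0167): 84 per group, 105 after loss; or 66.8% power with 64.

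The Bonferroni figures assume the same effect size of 0.5 on each score.

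**The case against.** The strongest reply is that the plan already points to one measure and one analysis. Sample size calls the SDQ primary for the power calculation and uses its total score. Analysis plans a longitudinal model, so the three follow-ups feed one model per outcome. The mention of ECBI intensity and problem scores may only describe the instrument, as the list of SDQ subscales does. This is also a journal article without its analysis plan, where the model contrast and the handling of multiplicity are commonly set out.

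Much of this stands. A reader might infer that success on any of nine score-by-visit tests would count, and so quote an error of 23-29%. The documents do not support that. They plan no separate visit-level tests and state no any-one-wins rule. The figure also needs assumed correlations of 0.5-0.7 and counts results that favour usual care. The count of three primary scores is itself an inference, which is why the range starts at two tests. Nor is a success rule stated at all: had both instruments been required to succeed, the error would not exceed 5%, but power would fall below that for the SDQ alone.

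What remains is the identity of the primary outcome. It is stated in this document, with two instruments, and does not match the single score behind the sample size. That is more than a detail left to an unseen analysis plan.

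**Conclusion.** The point holds in this form: two instruments are primary in Outcome measures, one SDQ score at an unadjusted two-sided 5% supports the sample size, and no time point or model contrast is designated as the primary test.

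With one longitudinal test at 5% per instrument or score, the chance of at least one false-positive primary result is about 8-14%, roughly two to three times the nominal level, with about half of it in favour of the intervention. This assumes two to three tests, correlations from 0.7 down to 0, and that any one significant primary would be reported as success. Only if any of nine visit-level tests could count, a rule that is nowhere written, would it be about 18-37% (correlations 0.8 down to 0).

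**What to change.** In Outcome measures, name the SDQ total problems score as the single primary outcome. In Analysis, state the one between-arm contrast from the random coefficient model that tests it. The difference at twelve months is one acceptable choice: it fits the long-term aim in Background and in Strengths and limitations. One prespecified contrast over the whole follow-up would serve equally to hold the error at 5%.

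Make the ECBI intensity and problem scores, the SDQ subscales and the other time points secondary, reported with confidence intervals. If the ECBI is to keep confirmatory standing, test it in fixed sequence, only after SDQ total is significant.

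The change is to the text and needs no more participants, since the calculation was made for one test of SDQ total. The small downside is that an effect seen only on the ECBI, or only outside the chosen contrast, can no longer carry the claim of effectiveness.
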